#### Survey

Post implementation of the survey previously done in Phase B will be repeated to explore changes in knowledge, attitude, perceptions, current beliefs, and perceived practices regarding delirium management of intensivists, physicians, and ICU nurses from the participating ICUs [29],[31],[32].

#### Main outcome measures

The primary outcomes of the prospective before-after pilot implementation study are adherence to screening and (non)pharmacological treatment as described in the Dutch ICU delirium guideline. Adherence to the delirium screening procedure will be calculated as the percentage of performed assessments per day, relative to the total number of assessments that should have been performed (i.e. a minimum of three times daily in every patient). Successful implementation is defined as adherence to assessment of more than 85%. Delirium experts (expert raters) will conduct accuracy spot-checks during the intermediate and after periods on a random sample of the bedside nurses' screening assessments. The expert will then share his or her findings from the CAM-ICU or ICDSC assessment with the bedside nurse and point out any mistakes or misconceptions in the nurse's assessment. Cohen's kappa and 95% CIs will be used to analyze agreement of CAM-ICU/ICDSC assessments between the bedside nurses and the delirium experts.

Adherence to the following aspects of non-pharmacological and/or pharmacological interventions and prevention interventions (based on the guideline) will be assessed: a) pharmacological: prescription of antipsychotic drugs (e.g. haloperidol); b) non-pharmacological: attention to orientation, prevention of sleep deprivation, and the use of glasses and hearing aids; and c) prevention: adherence to early mobilization and physiotherapy. Data on adherence indicators will be collected from systematic registration in the patient data management system and direct observations.

The secondary outcomes are the process measures (as defined in the section process evaluation, e.g. incidence of delirium; delirium knowledge of nurses and physicians; interrater reliability of delirium assessment (CAM-ICU or ICDSC); hospital mortality in the before, intermediate, and after periods).

#### Other variables

During all measurement periods, data will be collected on: psychoactive drugs (psychiatrist, neurologist, or geriatrician consultations), complications (self-removal of endotracheal tube, central lines, feeding tubes, and falls out of bed) and length of ICU stay, length of hospital stay, mortality, and institutionalization after hospital discharge. These data are needed to explore a cost benefit analysis of completed implementation. Furthermore, severity of illness scores (APACHE II score) and ICU ward specialty (e.g. internal medicine, surgery, or combined) will be retrieved from the Dutch National Intensive Care Evaluation (NICE) registry with consent from the participating ICUs.

#### Analysis

Results are expressed as percentages. Adjusted analyses will be done using repeated measures analysis for binary outcome data. Finally, outcome differences between the ICUs adjustments for patient mix (e.g. age, diagnosis, APACHE II score) and ICU level will be assessed using multi-variable analysis.

#### Sample size

Based on the literature, the adherence rate to screening with the CAM-ICU or ICDSC could increase from 70%-85%, following implementation [31],[40]. Consequently, the sample size will be 924 patients (231 patients in the before period and 693 in the after period (3 periods, Figure 1)). The alpha level of significance is set at 0.01 (two-tailed) and the beta level at 0.90.

#### Process evaluation

A process evaluation can give insight into determinants or indicators of potential success or failure of a tailored implementation strategy [41],[42]. For this purpose, process data will be collected for each of substrategies within the ‘tailored strategy’.

We will conduct in-depth qualitative interviews with clinicians (*n*?=?12) from participating ICUs to understand their perceptions of the study’s effect on local practice and the effectiveness of individual components of the intervention. We will recruit these individuals by invitation letters sent to all six ICUs. A semi-structured interview guide will be developed to facilitate the interviews. The process evaluation will provide insight in elements of the tailored strategy that are less feasible and need refinement before further implementation. In a post-implementation survey, we will examine whether earlier barriers are removed and facilitators are taken up.

#### Process measures

Education: number of nurses attending per ward, duration of training per ward, evaluations of nurses attending the training, experience with the training;Tailored strategy: elements of the strategy are delivered as agreed; feasibility of the strategy, user experiences with the strategy, degree to which barriers are solved, and facilitators are used.

Other process indicators will be defined after the strategy procedure has been developed.

Data will be collected from questionnaires, interviews, and direct observations. The process indicators will be related to relevant outcomes (e.g. mortality reduction) of the ‘tailored strategy’ to identify elements of the strategy that were particularly associated with the success of the implementation.

#### Economic evaluation

Prolonged admission on the ICU due to delirium is related with increased health care costs. Therefore, strategies that focus on increasing adherence with the Dutch delirium guideline are likely cost-effective [15]. The economic evaluation compares usual care (before) and care after implementation of the guideline. The aim of this analysis is to explore whether the likely overall cost saving from the tailored guideline implementation strategy exceeds the overall cost of the tailored guideline implementation process.

#### Cost analysis

The economic evaluation will be performed from a health care perspective and in accordance with guidelines for such analysis [43]. Care costs of each strategy are defined as all direct medical costs associated with procedures performed within that strategy. The resources consumed by the implementation strategies will be assessed in the clinical study by collecting data on personnel costs (time spending for the strategy delivery team, for the nurses attending the strategy related activities, and for systematic screening), material costs (antipsychotic drugs), and overhead costs. Medical costs will be estimated by multiplying resource utilization with the cost per unit of resource (market prices, guideline prices, or self-determined prices based on costing methods, i.e. full costing) [43]. The implementation process and consequent costs will be estimated by focusing on activities performed with costs accumulated at the activity level(s) of the health care implementation processes. The incremental costs will be determined by the difference in resource consumption between usual care and tailored implementation. The economic analysis will be a cost-minimalization analysis, in which we investigate whether the likely overall cost saving from the tailored guideline implementation strategy exceeds the overall cost of the tailored guideline implementation process.

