**Discussion:**

Little is known on effective implementation of delirium management in the critically ill. The proposed multifaceted implementation strategy is expected to improve process measures such as screening adherence in line with the guideline and may improve clinical outcomes, such as mortality and length of stay. This ICU Delirium in Clinical Practice Implementation Evaluation study (iDECePTIvE-study) will generate important knowledge for ICU health care providers on how to improve their clinical practice to establish optimum care for delirious patients.

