### Phase D: implementation study

#### Study design and population

The impact of implementation of a delirium guideline in six ICUs for adults will be studied in a pilot feasibility study using a prospective multi-center before-after study design (Figure 1). The primary aim will be to evaluate to what extent a guideline implementation program can achieve changes in ICU professionals' clinical practice with regard to delirious patients. This will be measured by the degree of adherence to the guideline recommendations. A secondary aim will be to evaluate the impact of the implementation interventions on clinical outcomes (hospital mortality and length of stay at ICU) and costs of the implementation and whether these may be linked to the practice changes achieved. A before-after study is considered a useful instrument, particularly for pilot studies in which interventions are initially evaluated and refined if necessary before the testing of the implementation strategy on a wider scale is justified.

Implementation of the delirium guideline will be two-phased. First, we will implement delirium screening with the CAM-ICU or ICDSC. This is an essential first step because prevention and treatment of delirium will only be possible after adequate and early recognition. Second, protocolled prevention and treatment interventions (pharmacological and non-pharmacological) will be implemented. ICUs will be free to select either tool based on local preference.

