## Discussion

The goal of the iDECePTIvE study is to identify barriers and facilitators for adherence to a national ICU delirium guideline. We will analyze the current practice (Phase A) before executing the survey and focus group interviews to avoid a possible Hawthorne effect (attention effect) by which members of the focus groups could be influenced. Based on these results, a tailored implementation strategy targeting these influencing factors will be developed for successful implementation and long-term adherence to the guideline. Finally, a before-after multicenter study will be conducted to evaluate the impact of the implementation strategy on clinical practice including a cost-effectiveness analysis and the effects on clinical outcomes.

This study is unique in that it includes all components of a multifaceted implementation in a large cohort of critically ill patients and includes measurement of important clinical outcomes based on a national database benchmarking outcomes of intensive care in the Netherlands. In a systematic review of the literature, we found that ICU delirium implementation studies mainly focus on implementation of screening or assessment tools for early recognition of delirium in ICU patients and tend to ignore improvement of prevention and treatment [44]. Most implementation strategies were not based on a systematic analysis of the context, including barriers and facilitators. Studies have shown that large-scale implementation of a delirium screening tool in the ICU is both feasible and sustainable with a compliance rate that may exceed 80% [31],[40],[45]-[47]. However, these studies focused only on screening and not on pharmacological and non-pharmacological treatment of delirium. Furthermore, the analysis of the barriers and facilitators was unstructured and not focused on treatment as proposed in the current delirium guideline. In this proposed study, the multifaceted strategy will be based on theoretically underpinned mechanisms to accomplish improved adherence to a guideline on ICU delirium. A study including all these components and of this magnitude has not been performed previously. Also, outcome assessments and cost-effectiveness analysis have not been performed on this scale.

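### The economic evaluation is fixed as cost-minimisation, which presumes equal outcomes; the protocol expects outcomes to change and elsewhere calls the same evaluation cost-effectiveness and cost benefit

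*Protocol article*

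**What the plan says.** Cost analysis fixes the method: "The economic analysis will be a cost-minimalization analysis, in which we investigate whether the likely overall cost saving" is larger than what the implementation itself costs. The quantity compared is cost alone: "The incremental costs will be determined by the difference in resource consumption between usual care and tailored implementation". Economic evaluation sets the contrast: "The economic evaluation compares usual care (before) and care after implementation of the guideline". It also names longer ICU admission due to delirium as the reason costs rise.

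The resources itemised in Cost analysis are staff time for delivering the strategy, for attending its activities and for screening, followed by "material costs (antipsychotic drugs), and overhead costs".

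On outcomes, the abstract says that the strategy "may improve clinical outcomes, such as mortality and length of stay". Phase D, Study design and population, states: "A secondary aim will be to evaluate the impact of the implementation interventions on clinical outcomes (hospital mortality and length of stay at ICU"). Main outcome measures lists delirium incidence and hospital mortality among the secondary outcomes. The Discussion hypothesises that recorded delirium will rise with screening, expects it to fall with prevention and management, and gives less delirium and better patient outcome as the final goal.

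Two other places name the evaluation differently. The Discussion says the before-after study is "to evaluate the impact of the implementation strategy on clinical practice including a cost-effectiveness analysis and the effects on clinical outcomes", and later presents cost-effectiveness analysis on this scale as new. Other variables lists complications, ICU stay, hospital stay, mortality and institutionalisation, and adds: "These data are needed to explore a cost benefit analysis of completed implementation".

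**The concern.** Cost-minimisation, cost-effectiveness and cost-benefit analysis are different methods with different outputs. The first reports a cost difference and rests on equal effects. The second relates a cost difference to an effect difference. The third values effects in money. The protocol uses all three names for one evaluation and fixes the one whose premise its own hypotheses contradict.

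Two things are at stake. First, a cost-only result could be published as evidence of cost-effectiveness, which it cannot be. Second, cost alone is ambiguous when mortality may change: a patient who dies early uses fewer ICU days, and a patient who survives because care improved may use more. A third, smaller matter is that the section defining the costing does not say that stay and complications will be costed, although stay is the mechanism through which a saving is expected.

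**Working it through.** The point rests mainly on setting sections side by side. The arithmetic serves only to show that the study could not establish equal outcomes.

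**1. What the method needs.** Let ΔC be the cost after minus the cost before, and ΔE the corresponding change in health outcome. Choosing the cheaper strategy from ΔC alone is justified when ΔE = 0.

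**2. Does the protocol take ΔE = 0?**
- Delirium incidence: the Discussion expects a rise from screening and a fall from prevention and management. It predicts change in both directions, not equality.
- Hospital mortality: the abstract says it may improve, and Phase D evaluates it as a secondary aim. This is a possible change, not an assumed zero.
- ICU stay: also evaluated, but it is mainly a cost driver and can sit inside a cost comparison. It does not carry the argument.
- No section states, justifies or plans to test equality of outcomes.

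**3. Could a null mortality result supply the premise?** The only sample size given is for screening adherence, 70% to 85%, two-sided alpha 0.01, with the stated beta of 0.90 read as power.

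n per period = [z(0.995)·√(2·p̄·(1−p̄)) + z(0.90)·√(p1(1−p1) + p2(1−p2))]² / (p2−p1)², with p̄ = (0.70 + 0.85)/2 = 0.775

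= [2.576·√0.34875 + 1.282·√0.3375]² / 0.15² = (1.521 + 0.745)² / 0.0225 ≈ 228.1, rounded up to 229.

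The protocol states 231 (power 0.904 for 231 against 231), and 4 × 231 = 924. The size is therefore reproduced to within 2 patients, and it is built to detect a difference in adherence.

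The document gives no mortality rate. Under assumed rates, treating patients as independent and comparing the 231 before patients with the 693 later ones:

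| Assumed hospital mortality | Power, two-sided 0.05 | Power, two-sided 0.01 |
|---|---|---|
| 20% to 15% | 0.43 | 0.23 |
| 15% to 12% | 0.23 | 0.09 |
| 20% to 18% | 0.10 | 0.03 |

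A non-significant mortality difference would therefore be likely even if mortality had changed, and could not be read as equality.

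**4. What cost alone does when mortality moves.** If an extra proportion d of patients die on day t instead of leaving on day s, mean stay changes by −d·(s − t). For any d > 0 and s > t this is negative and is booked as a saving. If d is negative (mortality improves), the sign reverses and survival is booked as a cost. The direction follows from the method. The documents give no d, s or t, so no amount is put on it.

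**5. What is costed.**
- Economic evaluation: the cost mechanism is prolonged ICU admission.
- Other variables: ICU stay, hospital stay, complications and institutionalisation are collected in all periods for the economic work.
- Cost analysis: itemises resources used by the implementation strategies, then refers in general terms to resource use multiplied by unit cost. It does not name bed-days or complications and does not refer back to Other variables.

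**The case against.** The strongest reply is that the calculation is sensible for the question asked. Objective, aim 3 and the fourth research question ask about costs. Economic evaluation asks whether savings outweigh implementation cost. Cost analysis answers that. The component is exploratory, in a self-described pilot. Mortality effects are worded as possible only, and the Discussion urges great caution with clinical outcomes. Hospital mortality will be reported in every period, so a rise in deaths would be seen next to the costs.

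Much of this stands. Saving against implementation cost is a coherent net-cost question. But caution about an outcome is not an assumption that it is unchanged, and a net-cost comparison is neither a cost-minimisation result nor a cost-effectiveness result. The Discussion announces the latter.

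Three stronger readings are tempting and are not supported:
- A reader might infer that no saving could appear, because Cost analysis lists only implementation resources. Other variables collects stay and complications expressly for the economic work, and the listed items can be read as the implementation side only. What holds is that the sections do not connect.
- A reader might infer that a cost-effectiveness question set as a study aim goes unanswered. The aims and research questions ask about costs; the cost-effectiveness analysis is announced only in the Discussion, beyond a passing remark in Economic evaluation that such strategies are likely cost-effective.
- A reader might want a number of ICU days falsely counted as saved. Any such number needs an excess mortality, a day of death and a length of stay that the documents do not give, and more deaths is the opposite of what the protocol hopes for.

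**Conclusion.** The point holds as a fault in the method named and in what may be concluded from it. The specified analysis rests on equal outcomes, which the protocol does not assume, cannot show at its size and in part expects not to hold. Delirium incidence carries this firmly and hospital mortality tentatively. One evaluation has three incompatible method names, and the method actually fixed cannot deliver the cost-effectiveness analysis announced in the Discussion. The costing section also leaves unstated whether the stay and complication data enter.

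The effect on the result cannot be sized from the documents. Its reach is limited to the economic evaluation; the primary adherence outcomes are unaffected. The change should be made, because it alters what the economic analysis may conclude and costs little. The conclusion assumes that the three names refer to one evaluation. The document describes only one.

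**What to change.** In Cost analysis, replace cost-minimisation with a cost-consequence analysis (or a cost-effectiveness analysis) that:
- costs ICU days, hospital days and complications from Other variables explicitly, together with the implementation costs already listed;
- reports incremental cost with its uncertainty;
- shows beside it the changes in adherence, delirium incidence and hospital mortality.

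Compare delirium between the intermediate and after periods. The before period relies on antipsychotic use and recorded diagnosis where no screening is done, so a before-after difference would mix detection with effect. If a cost-effectiveness ratio on delirium is wanted, take its costs from the same two periods.

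Use one name for the analysis in Other variables, Cost analysis and the Discussion.

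The minimum alternative is to call it a net-cost analysis, cross-refer from Cost analysis to the data in Other variables, and remove the cost-effectiveness claims from Economic evaluation and the Discussion.

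The cost is rewording and a little more analysis work. Stay, complications and mortality are already collected in all periods, and Cost analysis already names sources for unit prices. No change to sample size, data collection or the primary analysis is needed.

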### Ethical considerations

This study protocol was presented to the Medical Ethical Committee of the Erasmus University Medical Center (registration number: MEC-2012-063). An exemption was obtained as ethical approval for this type of study is not required under Dutch law. This study is registered in the Trial register, located at http://clinicaltrials.gov, under number: NCT01952899. Data collection will be in line with Dutch METC endorsed privacy regulations, ensuring that data collected for the analyses cannot be traced to individual patients by the coordinating investigators because the data will be anonymized by the local investigators who provide the data.

## Discussion

The goal of the iDECePTIvE study is to identify barriers and facilitators for adherence to a national ICU delirium guideline. We will analyze the current practice (Phase A) before executing the survey and focus group interviews to avoid a possible Hawthorne effect (attention effect) by which members of the focus groups could be influenced. Based on these results, a tailored implementation strategy targeting these influencing factors will be developed for successful implementation and long-term adherence to the guideline. Finally, a before-after multicenter study will be conducted to evaluate the impact of the implementation strategy on clinical practice including a cost-effectiveness analysis and the effects on clinical outcomes.

This study is unique in that it includes all components of a multifaceted implementation in a large cohort of critically ill patients and includes measurement of important clinical outcomes based on a national database benchmarking outcomes of intensive care in the Netherlands. In a systematic review of the literature, we found that ICU delirium implementation studies mainly focus on implementation of screening or assessment tools for early recognition of delirium in ICU patients and tend to ignore improvement of prevention and treatment [44]. Most implementation strategies were not based on a systematic analysis of the context, including barriers and facilitators. Studies have shown that large-scale implementation of a delirium screening tool in the ICU is both feasible and sustainable with a compliance rate that may exceed 80% [31],[40],[45]-[47]. However, these studies focused only on screening and not on pharmacological and non-pharmacological treatment of delirium. Furthermore, the analysis of the barriers and facilitators was unstructured and not focused on treatment as proposed in the current delirium guideline. In this proposed study, the multifaceted strategy will be based on theoretically underpinned mechanisms to accomplish improved adherence to a guideline on ICU delirium. A study including all these components and of this magnitude has not been performed previously. Also, outcome assessments and cost-effectiveness analysis have not been performed on this scale.

Furthermore, the results of this study will expectedly provide us with further knowledge on effective implementation of optimal care of the delirious patient at the ICU. We will provide answers to not only the ‘why should we implement’ questions, but also answers to ‘how to implement’ question and provide clues to reproducibility. In other words, the results of this study may help persuade clinicians and nurses to put effort into formal implementation of interventions, when indeed the results confirm that these may improve outcomes of our patients.

The results of this project will therefore add to the general body of knowledge about implementation science at the ICU. The knowledge generated from this study can also be of use in other improvement projects and guidelines in the ICU that require collaboration between different health care providers [48],[49].

A major limitation of this study with regard to the clinical outcomes assessment (mainly: mortality) is the before-after study design (phase D). Although changes in team behavior and clinical practices (i.e. guideline adherence; the primary outcome) related to delirium management during the course of this study are very likely to be due to the implementation itself, changes in mortality (secondary outcome) are less likely to be caused exclusively by the implementation. Other factors besides the implementation interventions that may impact on mortality include case-mix changes over the course of this study, changes in composition of the medical teams, or organizational changes (e.g. rebuilding of ICU). Such changes can only be partly accounted for in multivariable analysis because unmeasured (or unmeasurable) confounders are potential sources for bias. Therefore, results of the pilot before-after study on clinical outcomes rather than process measures should be interpreted with great caution. The generalizability is limited because concurrent changes in content or organization of care that may influence clinical outcomes may confound attribution of observed changes in outcomes to the implementation strategy. Furthermore, there is some evidence that suggests that uncontrolled before-after studies may overestimate the effects of quality improvement projects like this [24],[50]. In future studies, a stepped wedge cluster randomized trial would be a more sophisticated design, in which at the end of the study all participants will have received the intervention [51]. However, the current study with the proposed design will provide details regarding the feasibility of establishing practice changes and guideline adherence improvements with a tailored implementation and provide valuable information on successful and less successful implementation interventions and the need for their refinements in future studies on a wider scale. Future implementation studies aimed at improving outcomes will likely benefit from the knowledge generated by our study because effective interventions to change practice will be identified, which is a first essential step towards outcome improvement.

We hypothesize that the incidence rates of delirium in ICU patients will increase after implementation of early screening. One of the main reasons is that hypoactive delirium will be detected, which is ill-recognized without systematic screening. On the other hand, implementation of prevention and management of delirium is expected to decrease incidences. The balance between these opposite forces may explain why some studies found decreased incidences and others increased incidences of delirium after implementation of interventions targeted at delirium. Therefore, we propose a two-phased implementation process (Phase D: first screening implementation, thereafter prevention and treatment). After data collection for this reference period (before intermediate period), guideline-recommended treatment will be implemented. This approach prevents strong bias in the comparison of the incidence rates between the intermediate and after periods because assessment of delirium before and after implementation is similar.

The ultimate aim of our study is to reduce the incidence of delirium and improve the outcome for ICU patients and their families by implementing the national and international evidence-based guidelines on ICU delirium management. Furthermore, this study provides a framework for future efforts to stimulate guideline adherence and delirium management.

